**Methods/Design:**

CILON-T trial was a prospective, randomized, open-label, multi-center, near-all-comer trial to demonstrate the superiority of triple anti-platelet therapy to dual anti-platelet therapy in reducing 6 months' major adverse cardiovascular/cerebrovascular events, composite of cardiac death, nonfatal myocardial infarction, target lesion revascularization and ischemic stroke. It also tested whether triple anti-platelet therapy is superior to dual anti-platelet therapy in inhibiting platelet reactivity in patients receiving percutaneous coronary intervention with drug-eluting stent. Total 960 patients were randomized to receive either dual anti-platelet therapy or triple anti-platelet therapy for 6 months and also, randomly stratified to either lipophilic statin (atorvastatin) or non-lipophilic statin (rosuvastatin) indefinitely. Secondary endpoints included all components of major adverse cardiovascular/cerebrovascular events, platelet reactivity as assessed by VerifyNow P2Y12 assay, effect of statin on major adverse cardiovascular/cerebrovascular events, bleeding complications, and albumin-to-creatinine ratio to test the nephroprotective effect of cilostazol. Major adverse cardiovascular/cerebrovascular events will also be checked at 1, 2, and 3 years to test the 'legacy' effect of triple anti-platelet therapy that was prescribed for only 6 months after percutaneous coronary intervention.

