### Outcome measures

The primary endpoint of this study was the rate of MACCE, a composite ischemic vascular event following PCI, including cardiac death, nonfatal MI, TLR and ischemic stroke at 6 months in the DAT and TAT group. The key secondary endpoints defined a priori are

- P2Y12 reaction unit (PRU) as assessed by VerifyNow^® ^P2Y12 assay

- Cardiac death, nonfatal MI, TLR, target vessel revascularization (TVR), stent thrombosis and ischemic stroke

- MACCE according to the type of statin and its interaction with clopidogrel

- Bleeding, as defined according to the TIMI bleeding classifications [22], major bleeding defined by the presence of at least 1 of the following: intracranial bleeding (documented with magnetic resonance imaging, computed tomography, any other examination or autopsy), or clinically overt bleeding resulting in a 5 g/dL decrease in hemoglobin value (or, when hemoglobin values were not available, a 15% decrease in hematocrit).

- Angiographic outcome, such as late luminal loss, binary restenosis at 6 months' follow-up angiography

- Albumin-to-creatinine ratio

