### Statistical Analysis

#### Sample size calculation

To test the hypothesis that TAT is superior to DAT in reducing MACCE at 6 months after PCI, based on the previous outcome data [10,13,23], we assumed that MACCE rate in DAT and TAT group would be 10% and 5% respectively. Using a superiority design, an estimated total of 960 patients was needed to ensure a power of at least 80% to detect a 5% difference in the composite of ischemic vascular events between the two anti-platelet therapy groups using a two-sided t-test, with a sampling ratio of DAT:TAT at 1:1, bilateral risk set at 5% and drop-out rate estimated to be 10%.

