#### Statistical Analyses

All analysis will be done by intention-to-treat method (all patients analyzed as part of their assigned treatment group). However, per protocol (patients analyzed as part of their assigned group only if they actually received their assigned treatment) and as-treated analysis will also be performed solely for descriptive comparison.

The primary endpoint of 6 months' MACCE will be analyzed using χ^2^-test on an intention-to-treat analysis. The hypothesis will be evaluated based on a superiority testing. The clinical secondary endpoints will also be tested based on χ^2^-test, similarly as primary endpoint testing. The endpoints will be analyzed in pre-specified subgroups, which includes the presence of diabetes mellitus, long lesions (lesion length≥28 mm), small vessel lesions (lesion diameter < 2.75 mm), age and sex. Also, most importantly, post-hoc analysis of MACCE according to the type of statin given (atorvastatin vs. rosuvastatin) will be done. Analysis of platelet function will be tested using repeated ANOVA method with the Bonferroni's correction.

Continuous variables will be presented as mean ± SD and compared with the use of unpaired Student's t-test or in the case of non-normal distribution, Mann-Whitney U test. Categorical variables will be summarized as number or percentages and compared with χ^2 ^or Fisher's exact test, as appropriate. Survival curves using all available follow-up data will also be constructed for time-to-event variables using Kaplan-Meier estimates and compared by log-rank test. A p-value < 0.05 will be considered statistically significant.

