#### Secondary endpoints

Individual composites of MACCE

Platelet reactivity unit as assessed by Ultegra Rapid Platelet Function Assay (VerifyNow^®^)

MACCE according to the type of statin and its interaction with clopidogrel

Bleeding complications, as defined by TIMI classification

Angiographical outcome at 6 months' angiographical follow-up (late luminal loss, binary restenosis)

Albumin-to-creatinine ratio

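### The albumin-to-creatinine ratio is left to a generic two-group test that is valid but inefficient: it names no baseline adjustment, ignores the strata and gives no usable effect estimate for skewed data

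*Protocol article*

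**What the plan says.** All references are to the protocol article.

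- **Role of the endpoint.** The Abstract gives its purpose: "albumin-to-creatinine ratio to test the nephroprotective effect of cilostazol". Outcome measures lists ACR last under the sentence "The key secondary endpoints defined a priori are", and Appendix 1 repeats it among the secondary endpoints as "Albumin-to-creatinine ratio". The Background says that a renal effect has been seen in animals but not studied in people, and counts this among the questions the trial is to settle.
- **Method.** Statistical Analyses assigns a chi-square test to the clinical endpoints. Platelet function gets its own rule: "Analysis of platelet function will be tested using repeated ANOVA method with the Bonferroni's correction". ACR is not named. The general rule for continuous data is "Continuous variables will be presented as mean ± SD and compared with the use of unpaired Student's t-test". The same sentence allows a rank-based fallback when the data are skewed. The threshold is "A p-value < 0.05 will be considered statistically significant".
- **Not stated for ACR.** The article gives no measurement time, does not say whether a pre-treatment urine sample was taken, and does not say whether the compared variable is the follow-up value or a change. Randomization and interventions gives measurement times for platelet reactivity only.
- **Design factors.** The same section describes a second randomised allocation, to atorvastatin or rosuvastatin, and stratification by centre. The general rule uses neither.

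**The concern.** ACR is usually right-skewed and varies widely between patients. The trial enrols patients with and without diabetes (diabetes is a pre-specified subgroup), and Appendix 2 excludes advanced kidney disease by creatinine or dialysis but not by albuminuria. The stated rule fits such a variable poorly in three ways.

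1. The summary is mean ± SD even when the test switches to Mann-Whitney. For a skewed ratio, those two numbers are pulled by a few high values.
2. Mann-Whitney, as named, gives a p-value but no estimate of how much lower albuminuria is with triple therapy. A claim about nephroprotection needs that estimate.
3. No baseline value is named. If a pre-treatment ACR was collected and predicts the later one, leaving it out discards information.

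What is at stake is the precision and readability of one secondary result that the article presents as new evidence in humans.

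**Working it through.** **1. The plan's own figure.** Sample size calculation says "we assumed that MACCE rate in DAT and TAT group would be 10% and 5% respectively", with 80% power, two-sided 5%, 1:1 allocation and 10% drop-out.

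n per arm = (0.10×0.90 + 0.05×0.95) × (1.960 + 0.842)² / 0.05² = 0.1375 × 7.85 / 0.0025 ≈ 432

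432 / 0.90 = 480 per arm, so 960 in total. The figure reproduces. It was set for the composite clinical endpoint, and no calculation is given for ACR. The checks below use 432 evaluable patients per arm.

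**2. Cost of leaving out baseline.** Work on the log scale with SD set to 1. Let r be the correlation between baseline and follow-up log ACR. This is an **assumption**, shown as a range because the document gives no value. The SD that enters the comparison is:

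- follow-up value only: 1
- ANCOVA on baseline: √(1 − r²)
- change score: √(2(1 − r))

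The effect giving the follow-up-only test 80% power is 2.802 × √(2/432) = 0.191 SD. For ANCOVA it is 0.191 × √(1 − r²). At that smaller effect, the follow-up-only test has power Φ(2.802 × √(1 − r²) − 1.960). For r = 0.7 this is Φ(2.802 × 0.714 − 1.960) = Φ(0.04) = 52%.

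| Assumed r | Information discarded by follow-up only (r²) | ANCOVA power | Follow-up-only power | Log change-score power |
|---|---|---|---|---|
| 0.3 | 9% | 80% | 76% | 62% |
| 0.5 | 25% | 80% | 68% | 68% |
| 0.7 | 49% | 80% | 52% | 73% |
| 0.8 | 64% | 80% | 39% | 76% |

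The change score beats follow-up only when r exceeds 0.5, and never beats ANCOVA.

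**3. The same on a concrete scale.** Assume a log-SD of 1.2 and r = 0.7. The standard error is 1.2 × √(2/432) = 0.0816 without baseline and 0.0816 × 0.714 = 0.0583 with it.

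- Geometric mean 15% lower (−ln 0.85 = 0.163): power about 51% without baseline, 80% with it.
- Geometric mean 20% lower (−ln 0.80 = 0.223): power about 78% without baseline, 97% with it.

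**4. Cost of skewness.** This was simulated with log-normal data, log-SD 1.2, true ratio 0.80, 432 per arm and 2,000 runs per setting.

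| Assumed r | t-test on raw values | Mann-Whitney | t-test on logs | ANCOVA on logs |
|---|---|---|---|---|
| 0.5 | 46.6% | 75.2% | 77.0% | 88.6% |
| 0.7 | 49.2% | 78.0% | 79.4% | 96.9% |
| 0.8 | 50.6% | 76.4% | 79.0% | 99.4% |

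The first three tests do not use baseline, so their differences between rows are simulation noise. Mann-Whitney is 1.4 to 2.6 points below the log t-test. The fallback already in the plan therefore deals with nearly all of the skewness, and what remains is the gap to ANCOVA.

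**The case against.** The strongest reply is that ACR is never named in Statistical Analyses. A general sentence in a condensed article is being read as the model for one laboratory endpoint, and a full protocol or SAP may define the variable, the transformation and the covariates. This stands as a limit on the claim: it concerns what the article states, and it is met if another document already specifies the analysis. It does not remove the point. ACR is declared a priori, the other laboratory endpoint is given its own method, and the rule that is printed fits ACR poorly.

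Three stronger readings are tempting, and the document does not support them.

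- *That the plan would deliver the roughly 50% power of a raw-scale t-test.* For data this skewed, the plan's own wording leads to Mann-Whitney, at 75% to 78% in the simulation.
- *That the plan certainly ignores baseline.* An unpaired test on a change score also fits the sentence, and it would use baseline if one exists. The document does not say that one was taken.
- *That a chance imbalance in starting albuminuria would be taken for a drug effect.* Under randomisation, chance imbalance is already covered by the 5% error rate. The unpaired test is valid, only less precise.

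It is also fair that the renal question does not appear in the study objectives or in the Discussion section on the issues sought, and that ACR is listed last. This bears on priority, not on whether the wording should be improved.

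**Conclusion.** The point holds as one of efficiency and reporting, not of validity. The only stated rule reaching ACR names no baseline adjustment, omits the two design factors, summarises a skewed ratio by mean ± SD, and under Mann-Whitney gives no effect estimate.

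The size of the power loss rests on two things the document does not give: whether a pre-treatment ACR exists, and how strongly it correlates with the follow-up value. Against 80% for log-scale ANCOVA, a follow-up-only test has 76% at r = 0.3, which is a small loss, and 52% to 39% at r = 0.7 to 0.8, which is a large one. If no pre-treatment sample exists, changing the method adds only about 2 points, and the benefit is mainly an interpretable estimate. Leaving out centre and statin also costs some precision if they predict ACR; nothing in the document allows that to be sized.

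The change is worth making for a pre-declared secondary endpoint. The primary analysis and the 960 are not in question.

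**What to change.** In Statistical Analyses, add a rule for ACR alone, in place of the generic one:

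- Analyse log ACR at 6 months, by assigned group, in a linear model with treatment, randomised statin and centre. If a pre-treatment ACR was collected, add log baseline ACR as a covariate.
- Report the triple-to-dual ratio of geometric means with its 95% CI.
- Summarise ACR by geometric mean or median with a matching measure of spread, not mean ± SD.
- State when ACR was measured. Define baseline as a value obtained before any randomised treatment was given.
- If no such sample exists, use the same model without it and describe the result as a between-group difference at 6 months.

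**Cost.** A sentence or two of analysis wording, still possible because the analyses are written in the future tense. Patients without a baseline value will need a simple imputation of that covariate. The article reports that the 960 patients were already randomised, so a missing pre-treatment sample cannot be added now. The sample size and the primary analysis do not change.

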**Discussion:**

CILON-T trial will give powerful insight into whether triple anti-platelet therapy is superior to dual anti-platelet therapy in reducing ischemic events and platelet reactivity in the real-world unselected patients treated with drug-eluting stent for coronary heart disease. Also, it will verify the laboratory and clinical significance of drug interaction between lipophilic statin and clopidogrel.

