Additionally, there have been numerous questions as to whether there are significant interaction between clopidogrel and lipophilic statin and whether such interaction can be overcome by the addition of cilostazol. Although data on this matter is controversial but somewhat been in favor of being no significant in vivo interaction between clopidogrel and lipophilic statin [15], the interpretation and application of these data have been restricted by the unrandomized/unstratified manner of the studies [16-18] and non-prospective collection of the data [19]. Also, although the pleiotrophic effect of cilostazol in renal function has been demonstrated in some animal experiments [20,21], whether this holds true for humans have never been investigated.

In order to provide a definite answer to the above questions, we planned the 'Influence of **CIL**ostazol-based triple anti-platelet therapy **ON **Ischemic Complication after drug-eluting sten**T **implantation (**CILON-T**)' study. In this study, we compared the efficacy and safety of triple anti-platelet therapy (TAT), composed of aspirin, clopidogrel and cilostazol, with the conventional DAT by evaluating MACCE and platelet reactivity in an unselected population of patients receiving PCI with DES for coronary heart disease (CHD) in real-world practice. In addition, we would like to get answers for the issues whether lipophilic statin-clopidogrel interaction would influence the patient outcome and whether cilostazol can overcome such interaction, using atorvastatin (Lipitor^®^, Pfizer) dependent on cytochrome P450-3A4 (CYP3A4) for metabolism versus rosuvastatin (Crestor^®^, AstraZeneca) independent from CYP3A4.

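### Beyond a protected primary test, one p < 0.05 significance rule covers about 13 unranked key secondary comparisons, although some are described in confirmatory terms

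*Protocol article*

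**What the plan says.** All references are to the Protocol article.

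- **Primary test.** Outcome measures and Appendix 1 name one primary endpoint, 6-month MACCE. Sample size calculation ties the error rate to that endpoint alone: "bilateral risk set at 5% and drop-out rate estimated to be 10"%.
- **Secondaries.** Outcome measures opens its list with "The key secondary endpoints defined a priori are". It then names PRU, six clinical events, MACCE by statin type and its interaction, TIMI bleeding, angiographic outcome (late loss and binary restenosis as examples) and albumin-to-creatinine ratio.
- **How they are tested.** Statistical Analyses says: "The clinical secondary endpoints will also be tested based on χ^2^-test, similarly as primary endpoint testing". The section ends with "A p-value < 0.05 will be considered statistically significant".
- **Qualifiers that do exist.** In the same section, per-protocol and as-treated analyses are marked as descriptive only, platelet function gets a Bonferroni correction within a repeated ANOVA, and the MACCE comparison by statin is called post-hoc.
- **Later readings.** The abstract adds: "Major adverse cardiovascular/cerebrovascular events will also be checked at 1, 2, and 3 years to test the 'legacy' effect".
- **Wording attached to secondaries.** The abstract says "It also tested whether triple anti-platelet therapy is superior to dual anti-platelet therapy in inhibiting platelet reactivity", and Study objectives, hypothesis and design repeats the superiority question for platelet reactivity. The abstract's Discussion says "it will verify the laboratory and clinical significance of drug interaction between lipophilic statin and clopidogrel". Background introduces the trial with "In order to provide a definite answer to the above questions", where the questions include the statin and renal ones.

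**The concern.** Unadjusted secondary tests after one protected primary test are common, and acceptable when they are read as supportive. Here the article calls the secondaries key, tests the clinical ones in the same way as the primary, and calls any p-value below 0.05 statistically significant. It also describes two of them, platelet reactivity and the statin interaction, in terms normally kept for confirmatory results. Followed as written, the trial could miss its primary endpoint and still report a component, restenosis, renal or statin result as statistically significant under the same rule. The 5% error rate behind the sample size covers only the primary test.

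The statin comparison adds a contradiction. Outcome measures lists it among endpoints fixed in advance, while Statistical Analyses calls it post-hoc and, in the same sentence, the most important such analysis. Its evidential status is therefore not settled.

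**Working it through.** **1. Check that the primary test is sound.** Inputs from Sample size calculation: 10% versus 5%, two-sided 5%, 80% power, 1:1 allocation, 10% drop-out, total 960.

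n per arm = (1.960 + 0.842)² × (0.10 × 0.90 + 0.05 × 0.95) / 0.05² = 7.849 × 0.1375 / 0.0025 = 431.7, rounded up to 432.

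With drop-out: 432 / 0.9 = 480 per arm, total 960. The stated figure reproduces exactly. There is one comparison at 5%, so the primary error rate is not at issue.

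**2. Count the key secondary comparisons** (Outcome measures).

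| Endpoint | Comparisons |
|---|---|
| PRU | 1 |
| Cardiac death, MI, TLR, TVR, stent thrombosis, ischemic stroke | 6 |
| MACCE by statin type; interaction | 2 |
| Bleeding | 1 |
| Late loss; binary restenosis | 2 |
| Albumin-to-creatinine ratio | 1 |
| **Total** | **13** |

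The later MACCE readings and the subgroup analyses are left out of this count.

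**3. Chance of at least one p < 0.05 when every null hypothesis is true.** Under independence: 1 − 0.95¹³ = 48.7%. If PRU is set aside because of its Bonferroni correction: 1 − 0.95¹² = 46.0%.

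The document gives no correlations, so a common correlation is assumed. The figures below simulate 13 equicorrelated normal statistics.

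| Assumed correlation | Either direction | One direction only |
|---|---|---|
| 0 | 49% | 28% |
| 0.3 | 42% | 21% |
| 0.5 | 33% | 17% |
| 0.7 | 24% | 12% |
| 0.8 | 19% | 10% |

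The last column applies 0.025 to each test and approximates false results favouring TAT. The two statin comparisons have no such direction. Without them, independence gives 1 − 0.975¹¹ = 24.3%.

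**4. Allow for rare events.** Discrete tests on few events reject less often than 5%. Assume that cardiac death, MI, stent thrombosis, stroke and major bleeding are rare, with 480 per arm, and that Fisher's exact test is used when an expected count is below 5. The actual size per test is then 0.8% at an event rate of 0.5%, 1.9% at 0.75% and 2.9% at 1%. The independence figure becomes:

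- at 0.5%: 1 − 0.95⁸ × (1 − 0.008)⁵ = 36%
- at 1%: 1 − 0.95⁸ × (1 − 0.029)⁵ = 43%

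The event rates are assumptions, because the article gives none for the components.

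**The case against.** **Only an article is shown, and testing order is commonly left to an analysis plan.** This is fair as far as a missing hierarchy goes. The point rests instead on what the article does state: one significance rule for all tests, clinical secondaries handled like the primary, and firm wording attached to some of them.

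**The protected result is plain.** There is one working hypothesis, one primary endpoint, and an alpha and power tied to it. This stands. A reader might infer that the trial's 5% error rate is inflated. The documents do not support that, because the primary is a single comparison and its sample size reproduces.

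**A false positive is not shown to be likely.** This also stands. With 13 comparisons the figure stays below one half throughout the range, and it assumes no true effect anywhere. Correlation, rare events and counting only one direction all lower it.

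**The readings at 1, 2 and 3 years need not be three tests.** It is tempting to add them and reach 16 comparisons. The abstract says only that MACCE is checked each year for a legacy effect, and Statistical Analyses names a log-rank test on all available follow-up. Three separate tests would be an assumption, so they are not counted.

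**Qualifiers exist, and some of the language is soft.** The platelet analysis has its Bonferroni correction, the statin analysis is called post-hoc, and the main Discussion is more cautious about the statin question. The Bonferroni step, however, sits inside the repeated ANOVA and, as written, does not span endpoints. The post-hoc label conflicts with the list in Outcome measures, so it cannot serve as a clear exploratory label.

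**Conclusion.** The point holds in limited form. The primary test is protected at two-sided 5%. The secondaries are not: about 13 unranked key comparisons share its p < 0.05 rule, and two of the topics are described in confirmatory terms. If no true effects exist, at least one nominally significant secondary is expected in roughly 20% to 49% of such trials, against a nominal 5%. The range rests on assumed correlations of 0.8 down to 0. Rare-event testing lowers the upper end to about 36% to 43% under the assumed event rates, and false claims favouring TAT are about half as frequent. This is a matter of which results may be called significant, and it should be corrected. It does not threaten the primary conclusion.

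**What to change.** - In Statistical Analyses, restrict the closing significance sentence to 6-month MACCE, TAT versus DAT. Optionally allow PRU as a second step at two-sided 0.05, tested only if the primary is significant.
- Label all other secondary endpoints, and MACCE at 1, 2 and 3 years, as supportive or exploratory. Report them with estimates, 95% confidence intervals and nominal p-values, without a claim of significance.
- Give the statin analysis one status, the same in Outcome measures and Statistical Analyses.
- Soften the abstract's promise to verify the drug interaction and the Background's promise of a conclusive answer, so that each matches the status of its endpoint.

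The cost is a few sentences. The primary test, its alpha, the sample size and data collection are unchanged. The downside is that, if the primary test fails, a PRU or statin difference can be reported only as exploratory.
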